## Abstract

**Background:**

Preoperative anxiety in children is highly prevalent and is associated with adverse outcomes. Existing psychosocial interventions to reduce preoperative anxiety are often aimed at distraction and are of limited efficacy. Gradual exposure is a far more effective way to reduce anxiety. Virtual reality (VR) provides a unique opportunity to gradually expose children to all aspects of the operating theater.

**Objective:**

The aims of our study are (1) to develop a virtual reality exposure (VRE) tool to prepare children psychologically for surgery; and (2) to examine the efficacy of the VRE tool in a randomized controlled trial (RCT), in which VRE will be compared to care as usual (CAU).

**Methods:**

The VRE tool is highly realistic and resembles the operating room environment accurately. With this tool, children will not only be able to explore the operating room environment, but also get accustomed to general anesthesia procedures. The PREoperative Virtual reality Intervention to Enhance Wellbeing (PREVIEW) study will be conducted. In this single-blinded RCT, 200 consecutive patients (aged 4 to 12 years) undergoing elective day care surgery for dental, oral, or ear-nose-throat problems, will be randomly allocated to the preoperative VRE intervention or CAU. The primary outcome is change in child state anxiety level between baseline and induction of anesthesia. Secondary outcome measures include child’s postoperative anxiety, emergence delirium, postoperative pain, use of analgesics, health care use, and pre- and postoperative parental anxiety.

**Results:**

The VRE tool has been developed. Participant recruitment began March 2017 and is expected to be completed by September 2018.

**Conclusions:**

To our knowledge, this is the first RCT evaluating the effect of a VRE tool to prepare children for surgery. The VRE intervention is expected to significantly diminish preoperative anxiety, postoperative pain, and the use of postoperative analgesics in pediatric patients. The tool could create a less stressful experience for both children and their parents, in line with the modern emphasis on patient- and family-centered care.

**Trial Registration:**

Netherlands Trial Registry: NTR6116; http://www.trialregister.nl/trialreg/admin/rctview.asp?TC=6116 (Archived by WebCite at http://www.webcitation.org/6ryke7aep)

## Introduction

Fifty to 70% of children experience elevated levels of anxiety and distress prior to surgery [1,2]. Preoperatively, anxious children are more often agitated, sad, emotional, less cooperative, and more resistant compared to children who are not anxious [3,4]. Preoperative anxiety is also associated with a higher incidence of emergence delirium, more intense and prolonged pain postoperatively, and poorer recovery [3,5,6]. A child’s operation is also a stressful experience for parents and parental fear has been shown to intensify children’s preoperative anxiety [7,8]. Anxious children undergoing surgery, as well as their parents, are even at risk for a posttraumatic stress disorder [9]. These adverse outcomes underscore the urgent need to develop effective strategies to minimize preoperative anxiety in children.

Education programs have proven to be effective in reducing children’s preoperative anxiety. Nonetheless, a recent systematic review by Copanitsanou and Valkeapää indicated that education seems to have a negative effect on younger children’s anxiety [10]. Other complementary methods for reducing preoperative anxiety in children predominantly focus on distraction, for instance, watching a video, listening to music, playing video games, or distraction by clowns [11-14]. However, scientific literature shows that gradual exposure is a much more effective way to reduce anxiety in children than mere distraction [15]. Due to busy clinical practices and the daily use of surgery rooms, exposing children to all pre- and postoperative aspects is often not feasible.

Virtual reality exposure (VRE) offers the possibility to expose children of different ages to a highly realistic virtual environment that mimics the operating theater of a hospital. Children can get accustomed not only to the operating environment, but also to the procedures associated with anesthesia. VRE has already been shown to be effective as a treatment for specific phobias in children, such as a fear of heights or a fear of flying [16]. To the best of our knowledge, the efficacy of VRE to prepare children for general anesthesia and surgery has not yet been studied. Furthermore, Cochrane reviews showed that most studies examining interventions for induction of anesthesia in children are small and of poor quality [17,18]. As such, high-quality randomized controlled trials (RCTs) are needed.

The aims of the PREoperative Virtual reality Intervention toEnhance Wellbeing (PREVIEW) study are (1) to develop a VRE tool to prepare children for surgery; and (2) to conduct an RCT to test the effectiveness of the VRE tool in children undergoing elective day care surgery.

## Methods

### Virtual Reality Design

The VRE tool encompasses a highly realistic virtual environment that replicates the operating theater of the Erasmus MC-Sophia Children’s Hospital, Rotterdam, the Netherlands.

A multidisciplinary team, consisting of child life specialists, child psychologists, a child psychiatrist, anesthesiologists, a three-dimensional (3D) acting director, and a 3D project manager designed the script of the VRE. Working together with specialized virtual reality (VR) developers and animators, multiple 3D characters, asset, and environment artists created the scenery and character modeling.

During the design and development phases, team meetings were held to review the process and make any necessary adjustments. Overall, the main goal was to create a dynamic and interactive environment that will prepare children for surgery under general anesthesia, in a realistic and child-friendly manner. Once the VR software was created, it was pilot tested in healthy children (N=10). Based on the observations and responses of the pilot test, final adjustments were made.

### Technical Specifications

#### Hardware Details

All 3D characters in the virtual environment were modeled after pediatric anesthesiology employees who had undergone motion capture recording with professional Vicon Motion Systems Ltd equipment (Vicon Motion Systems Ltd). Vicon Vantage cameras were used for body motion capture and the Vicon Cara system, including 4 high resolution high speed cameras and a custom head rig, were used for facial motion capture.

The virtual environment is presented via an HTC Vive headset, using room-scale technology, which allows the user to navigate naturally. Real world awareness is created through a 110 degrees field of view for captivating immersion. The Vive features 32 sensors for 360 degrees motion tracking, a 2160 by 1200 combined resolution, and a 90 Hz refresh rate. With 2 wireless, motion-tracked handheld Vive controllers, each containing 24 sensors, users can interact with precision and experience immersive environments. The headset is connected to a custom computer with an Intel Core i7-5820K processor and a NVIDIA GeForce GTX 1080 graphics card.

#### Software Details

All software used is of professional quality and well known in the film, game, and VR industry. Vicon Blade II software, which is compatible with the Vicon camera systems, is used for body motion capture, whereas Vicon Cara Live and Vicon Cara Post are used for facial motion capture. Blade II provides real-time visualization, in which multiple range of motion sequences, and thus multiple people, can be captured simultaneously. Cara Live is used during setup and capture, while Cara Post automatically identifies and tracks the markers, applied on a human face, over time, creating a 3D point representation of the markers.

With RealityCapture, accurate and realistic 3D models are created out of photographs. 3ds Max and Maya 2016 are digital tools used for creating complex 3D animations and models. Autodesk MotionBuilder 2016 Service Pack 1 is also used for 3D character animation. Mudbox 2016 and Zbrush 4R7 are tools used for high resolution 3D sculpting. Everything comes together in the game engine Unreal Engine 4.13.

### Virtual Reality Storyline

The duration of the VRE intervention is approximately 15 minutes. We developed one version for 4- to 7-year-old children and one for 8- to 12-year-old children such that the explanations of the procedures can be attuned to the child’s developmental level. We used 8 as the cut-off point between the versions because this age represents a key period in children's brain development with respect to cognitive flexibility and information processing [19].

The VR storyline begins in the holding area, where the child is sitting on a hospital bed (Figure 1). A receptionist welcomes the child and shows him/her a video with extra information on a virtual tablet. The video explains that one of the child’s parents will stay with him/her all the time and shows the hospital gowns the child and parent will be wearing to surgery. After the video, the child in the hospital bed is transported into the corridor of the operating theater by an anesthesiologist and a nurse anesthetist (Figure 2). The bed is taken into the operating room via the surgery preparation room. The child can point at different instruments, such as the oxygen saturation monitor, blood pressure cuff, and anesthesia mask, with a motion tracked controller so that the nurse anesthetist can explain what they are used for (Figure 3). Next, the child moves itself onto the surgery bed where the anesthetic preparation takes place. These preparations are explained at this stage. The program is able to show both intravenous and inhalational induction. After induction, the operating room fades out and the recovery room fades in (Figure 4). Finally, the anesthetist nurse shows another video on a virtual tablet, which explains what kind of feelings the child might experience after surgery, such as pain or nausea.

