### Patient Recruitment and Procedure

Eligible patients and their parents will be informed about the study by phone and, if interested, receive the patient information folder (PIF) by email. Participation will be voluntary and all data will be anonymized. Both parents will be asked to provide written informed consent. Patients who are 12 years old will also be asked to provide written informed consent themselves. Children under 12 years old will give their permission orally.

After informed consent is provided, children will be randomly allocated to the VRE intervention (N=100) or CAU (N=100) group at hospital admission. Randomization will be stratified by age group (4- to 7- or 8- to 12-years-old), and type of surgery (ie, oral and maxillofacial surgeries, tonsil and adenoidectomy, tympanostomy tubes, or other ear surgeries). The researchers and operating staff will be blinded to group allocation. The research assistant will not be blinded, since he/she will be guiding the intervention. This will take place in a separate room, in the presence of an accompanying parent. Un-blinding takes place if patients are excluded from the study and after the final assessment of the last included patient.

Assessments will be carried out at the following time points: (1) T1, admission to the hospital, before possible intervention; (2) T2, after the VRE intervention or after CAU, in the holding area; (3) T3, during induction of anesthesia, in the operating room; (4) T4, postoperatively, in the recovery room; and (5) T5, 3 days after surgery, at home.

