**Figure 5 figure5:**
[figure not shown]
Flow chart of the study design with outcomes, instruments, and informants at each time point.

For the secondary outcome measures, repeated measures ANOVA will be conducted with situational parental anxiety at T1 and T3 as within variables and group as between variables. Also, repeated measures ANOVAs will be performed using postoperative pain at T4 (in the recovery room) and T5 (at home) as outcomes, with group as between variables. The effect of the intervention on emergence delirium at T4 will be examined with an analysis of covariance (ANCOVA). Age and sex effects will be accounted for in all analysis.

Multiple linear regression analyses will be performed with change in child state anxiety between T1 and T3 and change in pain between T4 and T5 as outcomes. Predictor variables (ie, socioeconomic status, age, sex, type of surgery, preoperative child, and preoperative parental trait anxiety) will be included into the linear models to identify which factors influence VRE efficacy.

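### The VRE effect is not estimated in the two age strata that receive different versions, and the regression meant to show whether age influences efficacy cannot do so

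*Protocol article*

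**What the plan says.** - **Intervention.** The Virtual Reality Storyline section of the protocol article describes one storyline of about 15 minutes, then adds: "We developed one version for 4- to 7-year-old children and one for 8- to 12-year-old children". The stated purpose is "such that the explanations of the procedures can be attuned to the child’s developmental level", and the split is fixed by age: "We used 8 as the cut-off point between the versions".
- **Allocation.** Patient Recruitment and Procedure uses the same cut: "Randomization will be stratified by age group (4- to 7- or 8- to 12-years-old), and type of surgery". Children are "randomly allocated to the VRE intervention (N=100) or CAU (N=100) group at hospital admission".
- **Treatment comparisons.** Statistical Analyses gives the primary model as a repeated measures ANOVA of child anxiety at T1 and T3, with VRE versus CAU as the between-subject factor. The other models also use a single group factor. On age, the section says only: "Age and sex effects will be accounted for in all analysis". No group by age-group term and no estimate by stratum is stated.
- **What influences efficacy.** The same section names a multiple linear regression for this purpose, with six predictors: socioeconomic status, age, sex, type of surgery, child trait anxiety and parental trait anxiety. Sample Size also speaks of six predictors and bases the number on 100 intervention patients. Group is not among the six.
- **Background.** The Introduction cites a review in which "education seems to have a negative effect on younger" children's anxiety.

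**The concern.** Because the strata coincide with the versions, each version already has concurrent randomised controls. The stated analyses do not use this. Adjusting for age removes the part of the outcome that depends on age in both arms. It does not estimate how the VRE-CAU difference varies with age.

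The article does intend to ask whether age influences efficacy, but the regression it names for this has no control arm in it. The trial's own question about age would therefore be answered by a coefficient that does not measure it.

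The Discussion foresees use in standard care and suggests added value for young children. A favourable pooled result could be carried to both age groups although most of the benefit arose in one. A disappointing pooled result could conceal a benefit confined to one.

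**Working it through.** **1. The plan's own figure.** Inputs from Sample Size: f = 0.25, two-sided alpha 0.05, power 0.85, four time points, N = 200. With a 3-df multivariate group-by-time test (denominator df 196) and noncentrality f²N = 0.0625 × 200 = 12.5, power is 0.848 and the N required is 202. With f²(N − 2) = 12.375, power is 0.845 and N is 204. The figure of 200 is reproduced within rounding. For two equal groups d = 2f = 0.5, and this value is used below.

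**2. What the regression estimates.** Let m(a) be the mean T1-T3 change at age a under CAU, and τ(a) the VRE effect at that age.
- Mean change in VRE children is m(a) + τ(a). A regression in VRE children estimates the age slope of that sum.
- Whether age influences efficacy is a question about τ(a) alone. It needs m(a) from the CAU arm, that is, a group by age term.
- Using both arms without that term would not help, because the age slope would then be an average over the arms.

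**3. What pooling can hide.** Let p be the share aged 4-7 (not given in the article, so assumed). The pooled effect is p·d(4-7) + (1 − p)·d(8-12). Effects are in SD units of the analysed change, with positive meaning benefit. Power is for a two-group test with 100 per arm.

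| p | d(4-7) | d(8-12) | Pooled effect | Pooled power | Interaction power |
|---|---|---|---|---|---|
| 0.5 | 0 | 1.0 | 0.5×0 + 0.5×1.0 = 0.50 | 0.94 | 0.94 |
| 0.7 | 0.8 | −0.2 | 0.56 − 0.06 = 0.50 | 0.94 | 0.90 |
| 0.5 | 0 | 0.5 | 0.25 | 0.42 | 0.42 |

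The first two rows are pooled successes with no benefit, or harm, in one stratum. The third is a real benefit in one stratum that the pooled test misses more often than not. The pooled powers are slightly optimistic, because unequal effects add some variance within the VRE arm.

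**4. What stratum estimates can deliver.** With n per arm in a stratum, the 95% half-width is 1.96·√(2/n), and power at d = 0.5 comes from the noncentral t with noncentrality 0.5·√(n/2). The interaction SE is √(2/n(4-7) + 2/n(8-12)).

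| Split (4-7/8-12) | Half-width, SD | Power at d = 0.5 | Interaction SE | Difference detectable at 80% | Power for 0.5 SD difference |
|---|---|---|---|---|---|
| 50/50 | 0.39 / 0.39 | 0.70 / 0.70 | 0.283 | 0.79 | 0.42 |
| 60/40 | 0.36 / 0.44 | 0.78 / 0.60 | 0.289 | 0.81 | 0.41 |
| 70/30 | 0.33 / 0.51 | 0.84 / 0.48 | 0.309 | 0.86 | 0.37 |

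The pooled half-width is 1.96·√(2/100) = 0.28. Stratum intervals are therefore √(100/50) = 1.4 times as wide with an even split. With 70/30 they are √(100/70) = 1.2 and √(100/30) = 1.8 times as wide.

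**5. Age against version.** No child of 4-7 receives the 8-12 version, and no child of 8-12 receives the 4-7 version. A difference between the stratum effects is therefore the sum of any age effect and any version effect on efficacy.

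**The case against.** **The pooled contrast is legitimate.** The article defines one VRE tool with one storyline, and only the explanations are said to differ. A reader might infer that two different programmes are being lumped together and that the pooled test is therefore invalid. The text does not support that. VRE versus CAU is a sound estimate of an age-tailored strategy, which is the stated aim. This objection stands in full, and the pooled test should remain primary.

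**Subgroup analyses belong in the SAP.** An SAP may exist and is not shown, and accounting for age does not strictly rule out an age-by-group term. Mere absence of a subgroup analysis from an article would be no finding. However, this article does state a method for finding what influences efficacy, and that method, as described, cannot do it.

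**The review cited in the Introduction concerns education programmes.** A reader might infer that the article itself expects VRE to raise anxiety in younger children. It does not say so, and its Discussion suggests added value for young children. The citation makes an age difference worth estimating and does no more.

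**Age and version are tied by design.** This is correct: pooling does not cause the confusion, and estimates by stratum do not cure it. A reader might hope that a step at age 8, fitted alongside a slope in age, would isolate the version. It would not. The authors chose 8 because they regard it as a key developmental period, so a step could occur there without any version effect.

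**A rule to adopt only a version whose own interval excludes no effect would misfire.** At a true 0.5 SD in both strata, both would pass with probability 0.70 × 0.70 = 0.49 under an even split, or 0.84 × 0.48 = 0.40 under 70/30. This also stands, and no such rule should be attached.

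**Conclusion.** The point holds in a limited form. The primary test is valid for the age-tailored VRE. The stated analyses, however, give no VRE-CAU estimate in either age stratum, and the regression intended to show whether age influences efficacy is built on intervention patients without a group term and cannot show it.

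The possible masking is material: a pooled 0.5 SD is compatible with 1.0 SD in one stratum and none in the other. Those effects are illustrations, and nothing in the documents says that they are likely. The calculations also assume the age split, d = 0.5 and a simple two-group comparison of change. If SD units are read as those of a single mYPAS measurement, the figures correspond to a T1-T3 correlation of 0.5, since the SD of change is then √(2(1 − 0.5)) = 1 such unit.

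The stratum results will be imprecise. An interaction test that is not significant would be weak evidence of equal effects, because a 0.5 SD difference would be missed about 60% of the time (1 − 0.42 = 0.58 to 1 − 0.37 = 0.63).

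**What to change.** Before unblinding, add the following to the analysis plan:

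- Keep the pooled VRE-CAU comparison as the primary test.
- In the primary mYPAS model, using both arms, add group by age group (4-7, 8-12) for the T1-T3 change. In the repeated measures ANOVA this is the group by time by age-group term, with its lower-order terms.
- Report the VRE-CAU difference with a 95% CI in each stratum, and the interaction estimate with its CI and test. Label all of these as supportive and state their limited power.
- State that a difference between strata may reflect age, version or both, and that the design cannot separate them.
- If the predictor regression stays in intervention patients, describe it as predicting change among children given VRE, and do not present it as showing what influences VRE efficacy.

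The cost is a few lines of plan text and one set of model terms, with no new patients or data, since the stratification already supports the analysis. The drawback is precision: stratum intervals are about 1.4 times as wide as the pooled one with an even split, and wider still in the smaller stratum if the split is uneven.

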**Figure 1 figure1:**
[figure not shown]
The virtual reality holding area.

**Figure 2 figure2:**
[figure not shown]
Transportation through the corridor of the operating theater in virtual reality.

**Figure 3 figure3:**
[figure not shown]
The virtual reality operating room.

**Figure 4 figure4:**
[figure not shown]
The recovery room in virtual reality.

### Study Design

The PREVIEW study is a single-center, single-blinded RCT carried out in the Erasmus MC-Sophia Children’s Hospital, by the departments of Child and Adolescent Psychiatry/Psychology, Pediatric Anesthesiology, and Maxillofacial, Dental, and Ear-Nose-Throat (ENT) Surgery. This RCT involves a psychosocial intervention (VRE preparation) versus care as usual (CAU) in 4- to 12-year-old children undergoing elective day care dental, oral, or ENT surgery (N=200). CAU involves children being recommended by their anesthesiologist during the preoperative screening consultation to watch the informative online movie of the Erasmus MC-Sophia Children’s Hospital about general anesthesia prior to surgery.

### Inclusion and Exclusion Criteria

Eligible participants are all consecutive pediatric patients (aged 4 to 12 years) undergoing elective day care surgery (ie, dental, oral, or ENT surgery) at the Erasmus MC-Sophia Children’s Hospital, between March 2017 and August 2018. Exclusion criteria are mental retardation, inability of parents to read or write Dutch, epilepsy, visual impairment, or poor general health, indicated by an American Society of Anesthesiologists (ASA) classification of IV or more.

### Patient Recruitment and Procedure

Eligible patients and their parents will be informed about the study by phone and, if interested, receive the patient information folder (PIF) by email. Participation will be voluntary and all data will be anonymized. Both parents will be asked to provide written informed consent. Patients who are 12 years old will also be asked to provide written informed consent themselves. Children under 12 years old will give their permission orally.

After informed consent is provided, children will be randomly allocated to the VRE intervention (N=100) or CAU (N=100) group at hospital admission. Randomization will be stratified by age group (4- to 7- or 8- to 12-years-old), and type of surgery (ie, oral and maxillofacial surgeries, tonsil and adenoidectomy, tympanostomy tubes, or other ear surgeries). The researchers and operating staff will be blinded to group allocation. The research assistant will not be blinded, since he/she will be guiding the intervention. This will take place in a separate room, in the presence of an accompanying parent. Un-blinding takes place if patients are excluded from the study and after the final assessment of the last included patient.

Assessments will be carried out at the following time points: (1) T1, admission to the hospital, before possible intervention; (2) T2, after the VRE intervention or after CAU, in the holding area; (3) T3, during induction of anesthesia, in the operating room; (4) T4, postoperatively, in the recovery room; and (5) T5, 3 days after surgery, at home.

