### Sample Size

To conduct a repeated measures analysis of variance (ANOVA) with 4 time points (ie, T1, T2, T4, and T5) for self-reported child anxiety, Cohen *f* of 0.25, an alpha of .05 (2-tailed), and a power of .85, a sample size of 200 patients is needed (100 patients per group). To perform regression analyses with 6 predictor variables, a small to medium effect size, and a power of .85, a sample size of 100 patients in the intervention group is sufficient.

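### The sample size has no allowance for loss, although exclusions after randomisation are foreseen and the analysis it was sized for needs every wave, including one at home

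*Protocol article*

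**What the plan says.** Under Patient Recruitment and Procedure, the protocol article states that "children will be randomly allocated to the VRE intervention (N=100) or CAU (N=100) group at hospital admission". The same section then says: "Un-blinding takes place if patients are excluded from the study and after the final assessment of the last included patient". Un-blinding presupposes an allocation, so the sentence foresees exclusion of children who are already randomised. It gives no grounds. The criteria under Inclusion and Exclusion Criteria are all eligibility criteria at entry.

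Under Sample Size, the calculation is for a repeated-measures ANOVA with "4 time points (ie, T1, T2, T4, and T5) for self-reported child anxiety", with "Cohen *f* of 0.25" and "an alpha of .05 (2-tailed), and a power of .85". The result is "a sample size of 200 patients is needed (100 patients per group"). No allowance for loss is mentioned. The last of the four waves is "T5, 3 days after surgery, at home".

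Under Statistical Analyses, repeated-measures ANOVA is also named for the primary outcome (mYPAS at T1 and T3), for parental anxiety (T1 and T3) and for postoperative pain (T4 and T5).

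**The concern.** Three statements do not fit together: some randomised children are expected to leave, the number randomised equals the number needed, and the chosen analysis drops any child with a missing wave. The sized analysis depends on T5, which is collected after day-care patients have gone home and is therefore the wave most likely to be missed. Any such loss takes the analysis below the power on which the sample size rests. Deleting incomplete cases also discards the T1, T2 and T4 scores of a child who misses only T5, and it acts in the same way on the T4-to-T5 pain analysis.

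The exclusion rule adds to this. As worded, it takes a child out and reveals the arm. It does not say that the T3 mYPAS is still collected, or that the child is still analysed in the allocated arm.

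**Working it through.** **Inputs from the article (Sample Size; Patient Recruitment and Procedure).** f = 0.25, alpha = 0.05, target power 0.85, two groups, four waves, 200 needed, 200 randomised. The article gives no correlation between waves, no sphericity value and no loss rate. The losses used below are assumptions.

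**Step 1: reproduce the stated number.** Take the group-by-time interaction, with the effect size in Cohen's convention and sphericity:

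- noncentrality λ = f² × N = 0.0625 × N
- df1 = (2 − 1)(4 − 1) = 3
- df2 = 3 × (N − 2)
- power = P(noncentral F > 95th percentile of the central F)

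At N = 200, λ = 12.5 with df 3 and 594, and power is 0.854. The smallest even N that reaches 0.85 is 200, so the stated figure is reproduced. Close variants (λ = f²(N − 2), or the multivariate form) give 202.

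**Step 2: power with fewer complete cases.** The same formula, with N now the number of children who have all four waves:

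| Assumed loss | Complete cases | λ | Power |
|---|---|---|---|
| 0% | 200 | 12.500 | 0.854 |
| 2% | 196 | 12.250 | 0.846 |
| 5% | 190 | 11.875 | 0.833 |
| 10% | 180 | 11.250 | 0.810 |
| 15% | 170 | 10.625 | 0.785 |
| 20% | 160 | 10.000 | 0.757 |

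At 198 complete cases (1% loss), power is 0.8497, already just under 0.85.

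**Step 3: the primary analysis.** For two waves (T1 and T3) at the same f, df1 = 1 and df2 = N − 2. Power is 0.940 at 200, 0.916 at 180 and 0.900 at 170. It stays at 0.85 down to 146 children, a loss of (200 − 146)/200 = 27%. Both waves are also observed in hospital on the day of surgery.

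**Step 4: could exclusions bias the primary comparison, and in which direction?** Suppose the most anxious 5% of the VRE arm were removed. For a normal score, the mean of the top 5% is 2.06 SD, so the mean of the rest falls by 0.05 × 2.06/0.95 = 0.109 SD on the score used for selection. A score correlated ρ with it falls by ρ × 0.109. The primary outcome is the change T3 − T1. With equal correlations ρ of 0.3, 0.5 or 0.7 (assumed):

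- Selection on T1 anxiety: the change shifts by (1 − ρ) × 0.109 = 0.08, 0.05 or 0.03 SD, against VRE, because the retained children start lower.
- Selection on T2 anxiety: T1 and T3 fall equally, so the shift is about 0.
- Selection on T3 itself: 0.08, 0.05 or 0.03 SD in favour of VRE. The VRE session is over before T3, so refusing or not finishing it cannot depend on the T3 score.

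**The case against.** The strongest objection is that the primary outcome is hardly touched. The four-wave calculation is for the self-reported VAS, a secondary outcome, and step 3 shows that the primary test has ample margin at the same f. This stands, and it limits the weight of the point. Even for the VAS, the cost is about two power points at 5% loss and about four at 10%.

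The zero margin also depends on the effect-size convention. Other standard conventions, which bring in the correlation between waves, need far fewer than 200 (for example 92 for the between-group effect at a correlation of 0.5). This stands as well. But those conventions do not reproduce the article's 200, and the one that does leaves no margin. It also assumes sphericity.

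An article may leave analysis sets and missing-data rules to a fuller document. That is fair, and their absence is not the point here. The point rests on what the article does state: exclusion after allocation, a named complete-case method, and a number needed equal to the number randomised.

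A reader might go further and infer that exclusions would fall mainly on the VRE arm, remove its most anxious children and so favour VRE. Only that arm has a headset session to refuse, and "The research assistant will not be blinded, since he/she will be guiding the intervention". The article does not support this. It does not say that an incomplete session is a ground for exclusion, that exclusion is decided with knowledge of the arm, or that excluded children leave the analysis. Withdrawn consent, cancelled surgery or ineligibility found late could occur in either arm. Step 4 shows that even one-sided exclusion of anxious children could shift the T1-to-T3 change against VRE or not at all.

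**Conclusion.** The point holds for the sized analysis. The stated 85% for the four-wave self-reported anxiety test is met only at essentially full retention. It falls to 0.83 at 5% loss, 0.81 at 10% and 0.79 at 15%. These figures assume complete-case analysis, sphericity, Cohen's convention for f and loss rates that the article does not give. Complete-case loss also affects the T4-to-T5 pain analysis; its power was not computed. The primary comparison keeps about 0.92 power at 10% loss if the same f applies.

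No bias in the primary comparison is shown. One-sided exclusion is an inference, and the direction of any resulting bias in the change score is undetermined. The exclusion sentence still deserves rewording, because it fixes removal and un-blinding without saying that follow-up and analysis as allocated continue.

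**What to change.** 1. **Statistical Analyses:** for outcomes that include T5 or have more than two waves (child VAS anxiety; pain at T4 and T5), replace repeated-measures ANOVA with a linear mixed model using all available waves, so that a child who misses one wave stays in.
2. **Sample Size:** state the power at a realistic completion rate, for example 0.81 for complete cases at 90%, and say that the figure refers to the secondary VAS outcome.
3. **Patient Recruitment and Procedure:** replace the un-blinding sentence with wording such as: *All randomised children are followed and analysed in the allocated arm. The T3 mYPAS is collected whether or not VRE was completed, and the assessor stays blinded when a child discontinues.*

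The cost is a little more analysis work, reliance on a missing-at-random assumption and a slightly less favourable power figure. No extra patients are needed. Keeping 200 complete cases by recruitment instead would mean randomising 200/(1 − 0.10) = 223 children at 10% loss, which the modest shortfall in a secondary outcome hardly justifies.
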